### Trial Protocol

#### Description of Trial Flow

Patients will be identified in the ICU through twice daily surveillance by the research coordinator or treating ICU physicians. Each patient’s eligibility will be verified by the use of a screening form that summarizes the inclusion and exclusion criteria. The patient needs to have been randomized within 24 hours of their admission to the ICU.

#### Outcomes

The primary outcome is to determine the number of episodes of hypoglycaemia and hypokalaemia, and compare this with the usual treatment (control) group.

Additional outcome measures used to determine safety will be duration of mechanical ventilation, duration of ICU and hospital stay, hospital mortality, and measures of renal, hepatic and haematological dysfunction. Antibiotic use will be used as a surrogate marker for nosocomial infections. Biochemical markers as specified in the protocol will also be measured to compare between groups.

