**Methods:**

This protocol summarizes the rationale and design of a randomized, controlled, single-center trial investigating the effect of mandatory insulin therapy versus usual care insulin therapy for those patients admitted for a stay of longer than 48 hours. In total, 109 critically ill adults predicted to stay in intensive care for longer than 48 hours consented. The primary outcome is to determine the safety of mandatory insulin therapy in critically ill patients using the number of episodes of hypoglycaemia and hypokalaemia per unit length of stay in intensive care. Secondary outcomes include the duration of mechanical ventilation, duration of ICU and hospital stay, hospital mortality, and measures of renal, hepatic, and haematological dysfunction.

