#### Informed Consent

Wherever possible, informed consent will be obtained from patients prior to randomization. It is recognized that in the majority of cases the patients will be unable to give informed consent due to alterations in level of consciousness caused by illness and therapeutic sedation. Although a relative cannot provide consent on behalf of a patient whose consent cannot be obtained, a written agreement stating no objection will be obtained from the patient’s relative. The relative will be given the information sheet making them aware that they can only offer an opinion as to whether they know if the patient would not have objected to taking part in medical research.

In the event that the relative cannot be spoken to in person, a verbal “no objection” will be obtained by telephone and randomization will be undertaken. Verbal assent will be obtained by the recruiting consultant or an individual with appropriate experience he/she nominates. The quality of consent will be ascertained from the responses given by the relative. Questions will be encouraged and the relative will have the opportunity to clarify any of the information given. Signed confirmation of the verbal assent will be sought, retrospectively, if practical.

Once the patient regains the capacity to comprehend the details of the study, they will be asked for permission to include their data in the study. If a patient or relative refuses consent/assent then the patient will receive the usual treatment as defined by the clinician responsible for the patient's care.

If a patient dies before regaining consciousness and the relative has given assent, the patient's data will be included in the study. The person taking consent will ensure that the patient (or the relative) receives a copy of the Consent/No Objection Form, and that a copy is placed in the patient’s notes. The original will be filed in the Trial Office. This process is in line with the Mental Capacity Act 2005 and has been approved by a UK Research Ethics Committee.

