#### Data Collection

Clinical data will be collected in a standardized way on a trial specific data form. Data will be transcribed from the patient’s notes or the clinical information system (Philips CareVue) by members of the PERMIT research team. Baseline measures of severity of illness (Acute Physiology and Chronic Health Evaluation II score, Sequential Organ Failure Assessment score) will be collected on admission, along with the demographics required to demonstrate equivalent groups.

All estimations of blood glucose and serum potassium, whether performed in the central laboratory or using near patient testing, will be collected from the clinical information system (CareVue). The doses of insulin, potassium, glucose, and antibiotics will also be collected. Nitrogen input will be estimated from the documented feed rates. Blood glucose levels will be monitored hourly, and 3-hydroxybutrate levels daily, using the Abbott system.

Blood and urine samples will also be taken from all randomized patients whilst they remain in the ICU. Specifically, blood samples will be taken at baseline (Day 1), Day 3, Day 5, Day 7 and Day 14. Urine collections will be taken over the preceeding 24-hour period on Days 3, 5, and 7.

Data are collected for the entire period of the patient’s stay in ICU. The hospital discharge date will be obtained from the local patient administration system (PAS) by the Trial Office. When a patient is transferred to another acute hospital, the discharge date will be requested from the receiving hospital. To enable collection of patient status 30 days after randomization, the PAS will be interrogated to determine the patient’s location at 30 days. For those patients that have been discharged, the patient’s General Practitioner will be contact by telephone to establish their location. There is no planned long-term follow up.

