#### Statistical Analysis

The principal comparisons will be between those allocated to usual care and those allocated to mandatory insulin (the “intention to treat principle”). The primary outcome variable will be the differences in the number of hypoglycaemic and hypokalaemia events between groups which will be compared by chi-squared tests. Differences between multiply measured continuous variables will be compared using analysis of variance. To allow for differences in length of stay between patients, wherever possible, variables will be converted to time-weighted averages if they are used as a single, between-group measure.

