#### Data Safety and Monitoring

Data relating to the safety of patients will be reviewed by an independent statistician ([name]) once 40 patients have been randomized to the trial. The data reviewed will specifically relate to: (a) serious unanticipated events (SAEs) and (b) deaths at 30 days (any cause)

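### Ventilation and stay durations serve as safety measures although death shortens them, and 30-day mortality, collected and monitored, is not a named outcome

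*Protocol article*

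**What the plan says.** The Outcomes section states: "Additional outcome measures used to determine safety will be duration of mechanical ventilation, duration of ICU and hospital stay, hospital mortality", followed by measures of organ dysfunction. The abstract lists the same items as secondary: "Secondary outcomes include the duration of mechanical ventilation, duration of ICU and hospital stay, hospital mortality". In both places the mortality outcome is hospital mortality.

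Four other sections bear on this:

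- **Informed Consent** keeps early deaths in the data set. The case is "If a patient dies before regaining consciousness and the relative has given assent", and such patients' data are included.
- **Statistical Analysis** makes one allowance for unequal stays: "To allow for differences in length of stay between patients, wherever possible, variables will be converted to time-weighted averages", where a variable serves as a single between-group measure.
- **Data Collection** plans a fixed-time check. "To enable collection of patient status 30 days after randomization", the hospital's patient administration system is searched, and "For those patients that have been discharged" the General Practitioner is telephoned. On transfers it says: "When a patient is transferred to another acute hospital, the discharge date will be requested from the receiving hospital".
- **Data Safety and Monitoring** has an independent statistician review serious events and "deaths at 30 days (any cause" once 40 patients are randomized.

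Neither the abstract nor the Outcomes section names 30-day mortality.

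**The concern.** A safety measure should get worse when patients are harmed. Time on the ventilator, in the ICU and in hospital all stop at death, so an arm with more early deaths can record less of each. A reader who takes a shorter duration as reassuring could then be misled when mortality differs between arms, which is when a safety measure is most needed.

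Time-weighted averaging does not help. It puts repeatedly measured quantities such as glucose on a common footing across different stays, but it cannot correct a duration that is itself the outcome.

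Hospital mortality is the natural companion measure, but its observation window closes at discharge. A patient discharged alive who dies before day 30 counts as a survivor, and a long-stay patient who dies in hospital after day 30 counts as a death. The window therefore differs between patients, and treatment could affect it through length of stay. A fixed 30-day window avoids this. The plan already seeks that information and uses it once for monitoring, but the text does not carry it into the comparison of arms.

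**Working it through.** The article gives no mortality rate, duration or power for these outcomes, and the recruitment target of 120 is a feasibility figure. There is no stated figure to reproduce. Everything below is illustration on assumed inputs, apart from the target of 120 and the 109 patients recruited.

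**Formula.** Let m be mortality, S the mean duration in survivors and D the mean duration in those who die. S and D are taken as equal in both arms, so the arms differ only in mortality.

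- Mean duration over all patients = (1 − m)·S + m·D
- Difference, higher-mortality arm minus the other = (difference in m)·(D − S)
- Event-free days to day 30, death scored 0 = (1 − m)·(30 − S)

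The sign of the duration difference depends only on whether D is below or above S.

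**Assumed case: m = 25% vs 35%, S = 8 days.**

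| D (days) | Lower-mortality arm | Higher-mortality arm | Difference |
|---|---|---|---|
| 3 | 0.75·8 + 0.25·3 = 6.75 | 0.65·8 + 0.35·3 = 6.25 | −0.5 |
| 8 | 0.75·8 + 0.25·8 = 8.0 | 0.65·8 + 0.35·8 = 8.0 | 0 |
| 12 | 0.75·8 + 0.25·12 = 9.0 | 0.65·8 + 0.35·12 = 9.4 | +0.4 |

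Event-free days are 0.75·22 = 16.5 vs 0.65·22 = 14.3, whatever D is.

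**Same mortality, S = 10 days.** The means are 8.25 vs 7.55 (D = 3), 8.75 vs 8.25 (D = 5), 9.50 vs 9.30 (D = 8), 10.0 vs 10.0 (D = 10) and 10.5 vs 10.7 (D = 12). Event-free days are 0.75·20 = 15.0 vs 0.65·20 = 13.0 throughout.

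**How often a single trial would show the wrong direction.** This was simulated with 20,000 trials, 60 patients per arm, lognormal durations (log-SD 0.8), S = 10 and mortality 25% vs 35%. The more lethal arm had the shorter mean duration in 68% of trials with D = 3, 63% with D = 5, 55% with D = 8 and 45% with D = 12. It had fewer mean event-free days in 84% to 85% of trials for every D. That stability is partly by construction, because death enters the score directly.

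**Would mortality alone correct the picture?** Power to detect 25% vs 35% at two-sided 0.05 is about 22% with 60 per arm (the target of 120) and about 20% with 109/2 = 54.5 per arm (the number recruited). A statistically clear mortality difference would seldom accompany a misleading duration result of this kind.

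**The case against.** The strongest reply is that the article only names the durations. It does not say they will be compared without regard to death, and an analysis plan could show them by survival status or treat death as a competing event. That stands as far as detail goes: the absence of a death-handling rule is no fault of a condensed article. What remains is the choice of measure. The text calls these durations safety measures, keeps early deaths in the data, and offers only an adjustment that cannot apply to them.

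The second reply is that deaths are not hidden. Hospital mortality is in the same sentence, 30-day deaths go to an independent reviewer, and the primary safety outcome is hypoglycaemia and hypokalaemia. This also stands. It makes the point moderate, and it rules out saying that the durations can never be interpreted.

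A reader might infer several stronger things that the documents do not support:

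- **That the durations will favour a harmful arm.** The table shows the effect vanishing when deaths come as late as survivors' discharge, and reversing when they come later. The documents do not say which applies.
- **That vital status is lost for transferred patients.** Data Collection says a discharge date will be requested from the receiving hospital. It does not say that nothing else is obtained.
- **That 30-day status is available for everyone.** It is planned for inpatients and discharged patients. Completeness is not shown, and the section speaks of location as well as status.
- **That 30-day mortality is excluded as an outcome.** The abstract's list is introduced as inclusive, and the SPIRIT schedule is a figure not shown. One can say only that the visible text does not name it.
- **That the named outcomes should be replaced.** Enrolment in this open-label trial ended in 2007 and analysis was underway at publication, so replacement would be a post hoc change of outcome.

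**Conclusion.** The point holds with moderate weight. As safety measures, the three durations are ambiguous because death shortens them. Under the assumed 25% vs 35% mortality with survivors at 8 days, the apparent effect runs from half a day in favour of the more lethal arm (deaths at day 3), through zero (day 8), to 0.4 days against it (day 12). Direction and size both rest on assumptions, including equal survivor durations in the two arms. The structural fact does not: a shorter duration does not distinguish recovery from death.

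Hospital mortality is a legitimate outcome and offsets part of the problem. Its window varies between patients, however, and the trial is too small for a mortality comparison alone to correct a misleading duration reliably. The fixed 30-day measure is planned and monitored but not named as an outcome in the text. These are supporting outcomes in an unpowered pilot, so the remedy is to add to them, not to discard them.

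**What to change.** 1. Add all-cause mortality at 30 days from randomization as a named safety outcome, reported as the between-arm difference with a 95% CI, beside hospital mortality. Report how many patients in each arm have known status at day 30.
2. Keep duration of ventilation, ICU stay and hospital stay as named, but present them by survival status.
3. Add, as supplementary analyses, days alive and free of ventilation, of ICU and of hospital to day 30, with death by day 30 scored 0 and a rank-based comparison.
4. Label items 1 and 3 as added after enrolment.

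The cost is mainly wording and analysis time, since ICU data, hospital discharge date and 30-day status are already planned. There are three downsides. The additions are post hoc in an open-label trial and must be read as such. Completeness of 30-day status is not shown. Event-free days may be incomplete for patients readmitted or transferred, because detailed data cover the stay in this ICU.

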#### Sample Size Justification

The study duration will be limited by funding, so a formal power calculation has not been performed. Instead, a recruitment target of 120 patients is set. It was felt that as the recruiting ICU had admitted 912 patients in the 12 months prior to the start of the trial, of which 270 stayed for 5 or more days this would be a realistic recruitment target.

#### Informed Consent

Wherever possible, informed consent will be obtained from patients prior to randomization. It is recognized that in the majority of cases the patients will be unable to give informed consent due to alterations in level of consciousness caused by illness and therapeutic sedation. Although a relative cannot provide consent on behalf of a patient whose consent cannot be obtained, a written agreement stating no objection will be obtained from the patient’s relative. The relative will be given the information sheet making them aware that they can only offer an opinion as to whether they know if the patient would not have objected to taking part in medical research.

In the event that the relative cannot be spoken to in person, a verbal “no objection” will be obtained by telephone and randomization will be undertaken. Verbal assent will be obtained by the recruiting consultant or an individual with appropriate experience he/she nominates. The quality of consent will be ascertained from the responses given by the relative. Questions will be encouraged and the relative will have the opportunity to clarify any of the information given. Signed confirmation of the verbal assent will be sought, retrospectively, if practical.

Once the patient regains the capacity to comprehend the details of the study, they will be asked for permission to include their data in the study. If a patient or relative refuses consent/assent then the patient will receive the usual treatment as defined by the clinician responsible for the patient's care.

If a patient dies before regaining consciousness and the relative has given assent, the patient's data will be included in the study. The person taking consent will ensure that the patient (or the relative) receives a copy of the Consent/No Objection Form, and that a copy is placed in the patient’s notes. The original will be filed in the Trial Office. This process is in line with the Mental Capacity Act 2005 and has been approved by a UK Research Ethics Committee.

#### Randomization

Allocation to a treatment arm will be made randomly. A Web-based specialist randomization service will be used (www.thesealedenvelope.com). Randomization will occur once a patient meets the inclusion criteria and has either consented to the trial or his/her relative (Personal Legal Representative) has provided verbal or written assent. When a member of the trial team logs onto the randomization service, basic descriptive information will be requested. The allocation will be minimized according to the patient’s gender. The requirement to titrate an infusion of insulin in one group and an infusion of glucose in the other group, using two different schedules, precludes blinding.

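### Allocation is minimised on gender alone, but the stated analysis leaves gender out: slightly conservative if gender is prognostic, and free to correct

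*Protocol article*

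**What the plan says.** The Randomization section of the protocol article opens with "Allocation to a treatment arm will be made randomly" and continues "A Web-based specialist randomization service will be used". It then says "The allocation will be minimized according to the" patient's gender. No other factor is named and no assignment probability is given. On timing it says "Randomization will occur once a patient meets the inclusion criteria and has either consented to the trial", or a relative has given assent. The same section explains that titrating two infusions, "using two different schedules, precludes blinding".

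Trial Design, Setting, and Patient Population confirms an open-label trial in one ICU. Description of Trial Flow has patients found by "twice daily surveillance by the research coordinator or treating ICU physicians".

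The Statistical Analysis section defines the primary outcome variable as "differences in the number of hypoglycaemic and hypokalaemia events between groups which will be compared by chi-squared tests". Multiply measured continuous variables are compared by analysis of variance. Gender appears in neither comparison.

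**The concern.** Minimisation forces the arms to be alike on gender. If gender is related to the outcome, the treatment difference then varies less from trial to trial than it would under simple randomisation. A test that ignores gender still uses the larger variance, so its standard error is too big and some precision already paid for in the design is lost. The usual remedy is to carry the allocation factor into the analysis.

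A second question comes from the design itself. With two arms and a single two-level factor, minimisation is much easier to follow than when several factors interact. If the scheme has no random element, any imbalance within a gender forces the next patient of that gender to the other arm. A central service conceals a list, but it cannot conceal an allocation that can be worked out from earlier ones. Entry also rests partly on judgement: the attending physician decides whether 48 hours or more of critical care will be needed, and staff decide when to approach a relative.

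**Working it through.** The protocol gives no figure on either point, so there is none to reproduce.

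**A. Effect of leaving gender out**

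Inputs: N = 120 (Sample Size Justification). Assumed: 1:1 allocation, one binary outcome per patient, 60% of patients in one gender, and event risks p0 (in the 40%) and p1 (in the 60%). The documents give no event risks by gender.

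The unadjusted test uses the variance P(1 − P), with P = 0.4·p0 + 0.6·p1. With gender balanced by design, the relevant variance is W = 0.4·p0(1 − p0) + 0.6·p1(1 − p1). The unadjusted standard error is too large by the factor √[P(1 − P)/W].

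- Risks 10% and 20%: P = 0.16; P(1 − P) = 0.1344; W = 0.036 + 0.096 = 0.132; factor √(0.1344/0.132) = 1.009.
- Risks 10% and 30%: P = 0.22; P(1 − P) = 0.1716; W = 0.036 + 0.126 = 0.162; factor √(0.1716/0.162) = 1.029.
- Risks 20% and 60%: P = 0.44; P(1 − P) = 0.2464; W = 0.064 + 0.144 = 0.208; factor √(0.2464/0.208) = 1.088.

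So the standard error is too large by about 1%, 3% and 9%. A simulation of 20,000 trials per setting, with deterministic minimisation on gender and a nominal 5% unadjusted chi-squared test, gave:

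| Event risk by gender (assumed) | Type I error |
|---|---|
| 15% and 15% (no gender effect) | 4.7% |
| 10% and 20% | 4.9% |
| 10% and 30% | 4.6% |
| 20% and 60% | 3.6% |

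The first row already falls a little below 5% with no gender effect. The shortfall is material only in the last row, and no row exceeds 5%.

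**B. Predictability, if there was no random element**

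Deterministic minimisation on one two-level factor at 1:1 amounts to blocks of two within each gender. The number of certain allocations is floor(men/2) + floor(women/2).

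- N = 109 (Results): exactly one of the two gender counts is odd, so the sum is (109 − 1)/2 = 54 whatever the split; 54/109 = 49.5%.
- N = 120 (target): the sum is 60 if both counts are even and 59 if both are odd. The mean is 59.5, or 49.6%.

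An observer with a full tally by gender is right on all certain allocations and on half of the rest: (54 + 0.5 × 55)/109 = 74.8%.

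With a random element no allocation is certain. Simulation (1,500 trials per setting) gives correct-guess rates of about 72.0%, 68.5% and 64.0% when the favoured arm has probability 0.9, 0.8 and 0.7, against 50% under simple randomisation. These rates barely change for gender splits from 50% to 70%.

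**The case against.** On the analysis: the Statistical Analysis section is a short summary in a condensed article, covariate adjustment is often left to a statistical analysis plan, and none is shown. Nothing in the article suggests that gender predicts hypoglycaemia or hypokalaemia. Events may also be few. The Discussion expects both risks to be low and cites 5.1% of patients with a glucose below 2.2 mmol/L in an earlier trial; at that rate, 0.051 × 109 is about 6 patients. Stratifying so few events gains little. All of this stands as a limit on the size of the point. It does not change the fact that the tests the article names omit the allocation factor, or that including it is free.

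On predictability, a reader might infer that about half the allocations were certain in advance. The article does not support that. It says allocation is made randomly, and it neither gives nor excludes a random element. The assignment probability is a setting that a condensed article commonly leaves to the full protocol. Inferring the next arm also needs a cumulative record by gender and arm, and the article does not say that recruiters held one. Screening of all admissions, a screening form, randomisation within 24 hours of admission, and allocation only after consent or assent all narrow the room for steering.

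A reader might go further and infer actual selection bias. If recruiters shifted severity by 0.2 SD in opposite directions whenever the next arm was certain, the arms would differ by 2 × 0.495 × 0.2 = 0.20 SD, about one standard error (0.19 SD at N = 109). That behaviour is wholly assumed, so the figure illustrates a possibility and is not evidence about this trial.

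**Conclusion.** The analysis point holds, and it is small. The stated comparisons ignore the only named allocation factor. The consequence is a slightly conservative test if gender is prognostic: 4.6% to 4.9% against a nominal 5% at moderate assumed gender effects, and 3.6% at a strong one. There is no excess of false positives. These figures rest on assumed event risks, an assumed 60:40 gender split, 1:1 allocation and a patient-level binary outcome.

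The predictability point holds only conditionally. If the minimisation had no random element, 54 of 109 allocations could have been inferred by someone keeping count. The documents do not show that this was so. Enrolment has closed, so only disclosure and a check on existing data remain.

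**What to change.** 1. Compare events between arms stratified by gender, for example by a Mantel-Haenszel test or a gender-stratified comparison of event rates, and add gender as a term in the analysis of variance models. Gender is already held as the minimisation factor, so this costs nothing. With very few events the gain will be slight.

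2. Report the assignment probability used by the randomisation service. This takes one sentence.

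3. Only if that probability was 1.0: use the allocation log to identify patients entered when their gender was unbalanced between arms, and compare baseline APACHE II between those predictably allocated to mandatory insulin and those predictably allocated to usual care (the Berger-Exner approach). The Data Collection section already provides for APACHE II on admission, so no new data are needed. With about 54 such patients the check has limited power, and a null result should be reported with its confidence interval.
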